### Plans to promote participant retention and complete follow-up {18b}

The RECIPE study follow-up duration is only 28 days. For participants who are discharged from the hospital before the day 7 or day 28 follow-up assessments, these will be conducted over the telephone to maximise participant retention and follow-up. For participants who deviate from intervention protocols, an attempt will still be made to collect all outcome data.

### Confidentiality {27}

All collected information concerning participants in this study will be treated as confidential and securely stored study site or using secure electronic platforms. All paper-based participant information is stored in locked filing cabinets in research facilities with limited access. All data collection, process, and administrative forms are identified by a coded participant identification number to maintain participant confidentiality. All records that contain names or other personal identifiers, such as informed consent forms, are stored separately from study records identified by code number. Data will only be disclosed with permission of the individual participant, or in compliance with the law. Access rights, as provided by the law available in each participating state, can be exerted at any time by all the participating patients.

### Plans for collection, laboratory evaluation and storage of biological specimens for genetic or molecular analysis in this trial/future use {33}

There are no plans for any future genetic or molecular analysis of biological specimens.

## Statistical methods

### Statistical methods for primary and secondary outcomes {20a}

All statistical analyses will be performed using STATA.

The primary efficacy outcome will be an intention-to-treat analysis, comparing the proportion of procedures requiring prophylactic blood component transfusion between the two randomised groups. The primary safety outcome will be a per-protocol analysis comparing the percentage of procedures associated with a procedure-related bleeding complication between the two groups. The secondary outcomes will either be analysed as intention-to-treat analyses (for survival), modified intention-to-treat (comparing specific blood products or transfusion-related side effects) and per protocol analyses (for procedure-related complications other than bleeding and hospital length of stay). The primary outcomes and secondary outcomes comparing proportions or percentages will be compared using chi-squared or Fisher’s exact tests. The secondary outcomes examining continuous variables will be compared using the Mann–Whitney test. A *p*-value less than 0.05 is considered statistically significant in a two-sided test.

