## Abstract

**Background:**

Patients with cirrhosis often undergo invasive procedures both for management of complications of their advanced liver disease, including treatment for hepatocellular carcinoma, as well as underlying comorbidities. Despite a current understanding that most patients with cirrhosis are in a rebalanced haemostatic state (despite abnormalities in conventional coagulation tests, namely INR and platelet count), patients with cirrhosis are still often given prophylactic blood components based on these conventional parameters, in an effort to reduce procedure-related bleeding. Viscoelastic tests such as Rotational Thromboelastometry (ROTEM) provide a global measurement of haemostasis and have been shown to predict bleeding risk more accurately than conventional coagulation tests, and better guide blood product transfusion in a number of surgical and trauma-related settings. The aim of this study is to assess the utility of a ROTEM-based algorithm to guide prophylactic blood component delivery in patients with cirrhosis undergoing invasive procedures. We hypothesise that ROTEM-based decision-making will lead to a reduction in pre-procedural blood component usage, particularly fresh frozen plasma (FFP), compared with standard of care, whilst maintaining optimal clinical outcomes.

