Up-to-date international clinical practice guidelines acknowledge the limitations of standard haemostatic tests, particularly prothrombin time/INR, in predicting procedure-related bleeding, and as a consequence, no longer recommend routine pre-procedural blood component prophylaxis based on these parameters [15–17]. Despite this, clinical practice has been slow to change, and patients with cirrhosis are still frequently given blood component products, based on their INR and platelet count abnormalities, in an attempt to reduce peri-procedural bleeding [18]. Although the overall risk of bleeding for patients with cirrhosis undergoing procedures remains low, particularly for low-risk procedures [19–22], there is a subset of patients who do bleed, which is likely to explain the clinician tendency to “correct” standard coagulation tests abnormalities with pre-procedural blood product administration that has continued regardless of guidelines recommending against it. This is despite an acknowledgement that there are significant risks associated with blood component therapy, particularly large-volume products such as FFP, including fluid overload, pulmonary oedema, allergic reactions, and elevation in portal pressure [23, 24].

It is imperative that an improved method of assessing procedure-related bleeding risk in patients with cirrhosis is developed and validated, so that blood products can be efficiently and effectively allocated in this patient population.

In recent years, ‘global’ coagulation tests, such as ThromboElastoGraphy(TEG) and Rotational Thromboelastometry (ROTEM) have been developed. Whereas platelet counts, INR and APTT measure only individual components of the haemostatic system, ROTEM and TEG measure the viscoelastic properties of whole blood to provide a measure of overall haemostasis, from clot formation to clot retraction and fibrinolysis [25]. These point-of-care tests provide quick results and have been used to assess coagulation and guide blood product transfusion in a number of surgical and trauma settings, including liver transplantation [26]. In these settings, these tests predict bleeding and thrombotic risks more accurately than conventional coagulation tests, are associated with a reduction in intra-operative blood loss, decreased rates of blood product usage, and improved mortality [27].

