Recently, there has been increasing interest in the use of these viscoelastic tests in liver disease outside of the transplant setting. Two randomised controlled trials have found that using TEG to guide prophylactic blood component transfusion in patients with cirrhosis undergoing invasive procedures resulted in decreased blood product use without affecting bleeding outcomes [28, 29]. Similarly, a randomised controlled trial found that using ROTEM to guide pre-procedural blood product transfusion in the cirrhotic *children* having invasive procedures led to decreased FFP and platelet use, with no significant difference in procedure-related bleeding [30].

We designed this study to assess the utility of a ROTEM-based algorithm to guide prophylactic blood component delivery in *adult* patients with cirrhosis undergoing invasive procedures. We hypothesise that ROTEM-based decision-making will lead to a reduction in pre-procedural blood component usage, particularly FFP, compared with standard of care. We anticipate that there will be no difference in bleeding complications between the two groups.

By attempting to establish the role of ROTEM in assessing coagulation status in patients with chronic liver disease, we hope to improve the identification of those patients with cirrhosis who are and are not at increased bleeding risk, and in turn, improve the identification of those patients who are most likely to benefit from blood component transfusion.

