### Sample size {14}

Previous studies using other global coagulation assays in patients with cirrhosis undergoing invasive procedures have reported a significant (at least 45%) reduction in the need for prophylactic pre-procedural transfusions [28, 29]. Assuming a modest 30% reduction in pre-procedural prophylactic use of blood products, and with a power of 90% and an alpha of 5%, and accounting for possible drop-outs and missing data of 10%, a total of 56 participants or procedures (28 in each arm) will be needed.

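### The primary safety outcome rests on a difference test in a trial sized only for transfusion, so a non-significant result would not show that bleeding is not increased

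*Protocol article*

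**What the plan says.** All references are to the protocol article.

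- **Outcome and analysis set.** The Outcomes section makes procedure-related bleeding the primary safety outcome, framed as a difference between groups. Section {20a} adds: "The primary safety outcome will be a per-protocol analysis comparing the percentage of procedures associated with a procedure-related bleeding complication between the two groups".
- **Test.** Section {20a} fixes it: "The primary outcomes and secondary outcomes comparing proportions or percentages will be compared using chi-squared or Fisher’s exact tests". The significance rule is: "A *p*-value less than 0.05 is considered statistically significant in a two-sided test".
- **Size.** The Sample size section works from a 30% fall in prophylactic transfusion at 90% power and 5% alpha, and concludes: "accounting for possible drop-outs and missing data of 10%, a total of 56 participants or procedures (28 in each arm) will be needed". It gives no bleeding rate and no power for bleeding. The Trial design section limits the superiority aim to blood component use.
- **Expected safety result.** The Background section states: "We anticipate that there will be no difference in bleeding complications between the two groups". The Abstract hypothesises less product use "compared with standard of care, whilst maintaining optimal clinical outcomes".
- **Expected frequency.** The Background section also says: "Although the overall risk of bleeding for patients with cirrhosis undergoing procedures remains low", most of all for low-risk procedures.

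**The concern.** The expected safety result is a null, and the test chosen takes that same null as its starting hypothesis. With few patients and few events, failing to reject is the likely outcome both when bleeding is equal and when it is moderately raised. The smaller the trial, the more easily the expected answer appears.

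The ROTEM arm may withhold product from patients who would normally receive it. A report of fewer transfusions alongside a non-significant bleeding comparison could be taken as evidence that withholding is safe, when the data might be compatible with a large excess of bleeding.

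**Working it through.** **1. Evaluable numbers.** The plan's total can be reproduced. Read the 30% reduction as 100% versus 70%. The control rate of 100% is inferred, because only patients who would normally be transfused are randomised. With unpooled variance, two-sided alpha 0.05 and power 0.90:

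n = (1.960 + 1.282)² × (1.0 × 0 + 0.7 × 0.3) / 0.3² = 24.5, so 25 per arm.

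25 / (1 − 0.10) = 27.8, so 28 per arm and 56 in total. Conversely, 28 × 0.9 = 25.2. About 25 per arm is therefore the working number for bleeding, and a per-protocol set could be smaller.

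**2. What Fisher's test needs at 25 per arm.** For k bleeds against 0, the two-sided p-value is 2 × C(25,k) / C(50,k).

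- k = 5: 2 × 53,130 / 2,118,760 = 0.0502, not significant (20% versus 0%).
- k = 6: 2 × 177,100 / 15,890,700 = 0.022, significant.
- Against 1 bleed, 7 are needed (p = 0.049).

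With all 28 per arm, 5 versus 0 is still not significant (p = 0.051).

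**3. Power.** Every pair of binomial counts was enumerated and the probabilities of pairs with p < 0.05 were summed. The documents give no bleeding rate, so all rates here are assumptions.

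| Control | ROTEM | Fisher, 25 per arm |
|---|---|---|
| 2% | 6% | 0.2% |
| 5% | 10% | 1.3% |
| 5% | 15% | 7.2% |
| 5% | 20% | 19.8% |
| 5% | 25% | 37% |
| 10% | 20% | 8.6% |
| 10% | 30% | 30% |
| 15% | 45% | 53% |

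At 28 per arm the figures for 5% versus 10%, 15% and 20% are 1.5%, 7.8% and 20.7%. Uncorrected chi-squared at 25 per arm gives 8%, 21% and 38% for the same three. With equal arms and fewer than 10 bleeds in total, the expected bleeds per arm are below 5, and Fisher's test would normally be the one used.

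**4. What an interval would show.** Newcombe 95% intervals for ROTEM minus standard of care, 25 per arm:

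| Bleeds, ROTEM vs standard of care | Interval (percentage points) |
|---|---|
| 0 vs 0 | −13.3 to +13.3 |
| 1 vs 1 | −15.9 to +15.9 |
| 2 vs 1 | −12.6 to +21.3 |
| 5 vs 0 | +2.6 to +39.1 |

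The first row can be checked by hand. The Wilson upper limit for 0/25 is z²/(n + z²) = 3.84/28.84 = 13.3%, and with no events in either arm this is also the limit for the difference. In the last row the interval lies wholly on the side of harm while Fisher's p is 0.0502, so the choice of primary summary can change what is reported.

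**The case against.** **No safety claim is planned.** A reader might infer that the trial intends to claim non-inferiority, or to read p>0.05 as proof of safety. The documents do not support that. The Objectives section says only that bleeding will be compared, the superiority aim covers blood component use, and the sentence on no difference is an expectation. This stands. What remains is a mismatch between a stated expectation and a test that cannot confirm it.

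**The result is not a foregone conclusion.** A reader might also infer that a non-significant result is nearly certain whatever the truth, or would follow even if bleeding tripled. That holds only at low assumed rates. Low-risk procedures are capped at 25–30% of the total, and the bleeding definition is broad (a haemoglobin drop, or need for transfusion, readmission or intervention), so a control rate above 5% is plausible. At 10% or 15% a tripling would be detected 30% or 53% of the time. The unconditional wording fails; low power against moderate harm does not.

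**Leave it to the analysis plan.** Interval methods and reporting language often belong there, and naming a test does not preclude an interval. But section {20a} already fixes the test and the significance rule for a primary outcome, and that choice is what is criticised.

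**The DSMB protects patients.** It receives serious adverse events, bleeding in particular, within 24 hours and reviews bleeding trends after 15 and 28 participants. That covers conduct, not how the final comparison is interpreted.

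**An interval will usually be inconclusive.** True at this size. It at least shows how much excess bleeding remains possible. Adding a non-inferiority margin now would help little: with 5% bleeding in both arms (assumed), 25 per arm gives about 13% power for a 5-point margin and 37% for a 10-point margin. A margin chosen after recruitment began, by a steering committee that includes investigators, could also be influenced by bleeds already seen.

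**Conclusion.** The concern holds in a limited form. A two-sided difference test at about 25 per arm is a poor primary summary for a safety outcome that is expected to show no difference. If control bleeding is about 5%, a doubling is missed about 99% of the time and a tripling about 93% of the time with Fisher's test. The weakness lessens as rates or harms grow. The conclusion rests on three assumptions: 10% loss as the plan allows, bleeding rates that are assumed because none is stated, and Fisher's test being used when events are few. The efficacy analysis and the sample size for it are unaffected.

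**What to change.** In section {20a}, and in the analysis plan where one exists:

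1. Make the primary safety result the bleeding risk difference, ROTEM minus standard of care, with a 95% confidence interval by a named method (Newcombe or Miettinen-Nurminen). The Fisher p-value may be kept as supporting information.
2. State that p>0.05 will not be reported as no difference in bleeding or as safety maintained.
3. Word the conclusion by the upper confidence limit, that is, the largest excess in bleeding still compatible with the data.
4. State that the trial is not sized to exclude a clinically relevant excess in bleeding.

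Do not add a non-inferiority margin at this stage. The cost is a change of wording and a weaker safety statement in the final report; no extra patients or data are needed.

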### Interim analyses {21b}

No interim analyses are planned.

### Methods for additional analyses (e.g. subgroup analyses) {20b}

There are no additional subgroup analyses planned at this stage. Given the RECIPE trial is an RCT, we are not adjusting for any variables.

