### Intervention description {11a}

All participants will have baseline pathology including standard coagulation testing and a ROTEM analysis.

ROTEM analysis will be performed by one of the investigators using the ROTEM-sigma device located at the study site, within 4 h of the participant’s blood draw. The ROTEM-sigma performs all analyses on citrated whole blood and will be run according to the manufacturer’s instructions. Each blood sample will be tested using four ROTEM assays with different reagents provided by the manufacturer: each of these assays evaluates overall clot formation and strength. The EXTEM evaluates clot formation mimicking the conventional extrinsic pathway, INTEM evaluates clot formation mimicking the conventional intrinsic pathway, FIBTEM evaluates the contribution of fibrinogen to clot formation, and APTEM which evaluates any antifibrinolytic effect. All other laboratory tests will be run by the Hospital pathology laboratories at the study sites.

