#### ROTEM-based intervention

For participants assigned to the ROTEM-based decision-making arm, the following ROTEM parameters will be used to determine whether pre-procedural blood product should be given (see Fig. 1 below):Clotting time using EXTEM (CT_EX_)Amplitude at 5 min using EXTEM (A5_EX_)Amplitude at 5 min using FIBTEM (A5_FIB_)

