### Outcomes {12}

The primary efficacy outcome is the difference in the proportion of procedures requiring prophylactic blood component transfusion, defined as the procedures before which any combination of FFP, platelets and/or cryoprecipitate is given to the participant. The primary safety outcome is the difference in procedure-related bleeding complications between the two groups. Bleeding complications will be defined in accordance with the International Society of Thrombosis and Haemostasis guidelines and include clinically significant bleeding with a ≥ 20 g/L drop in haemoglobin or requiring blood transfusion, readmission, or intervention [33].

The secondary outcomes are comparisons in the following between the standard of care and ROTEM-based decision-making arms: amount (in units) of individual prophylactic blood products (FFP, platelets, cryoprecipitate) given; transfusion-related side effects, procedure-related complications other than bleeding (e.g. thromboses, infection, organ damage) assessed at day 0, day 7 and day 28, hospital length of stay (in days), and survival (which will be further delineated into procedure-related or not). Hospital length of stay and survival will be assessed at day 28, which is the end of the trial.

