### Participant timeline {13}

We aim to investigate 56 interventions in cirrhotic patients with coagulation abnormalities at the study sites. We will recruit patients from both outpatient clinics and inpatient wards who are scheduled for an upcoming invasive procedure, and who would usually be considered for blood components as bleeding prophylaxis prior.

The schedule of enrolment, intervention and assessments is displayed in Fig. 2. All patients meeting eligibility criteria will have a blood sample taken within 24 h of their upcoming planned procedure (72 h for stable outpatients). If platelets and/or INR are within the range that the patient would normally be given FFP or platelet transfusion prior to the procedure as per standard of care (institution-based), ROTEM analysis will be performed, and the patient will proceed to the randomisation phase.

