**Fig. 2 Fig2:**
[figure not shown]
RECIPE schedule of enrolment, interventions, and assessments. *Within 24 h of procedure for inpatients and 72 h of procedure for outpatients

Enrolled patients will be randomised in a 1:1 fashion to either procedure-prophylaxis guided by standard of care or ROTEM-based protocol as follows:Patients in the standard of care arm will receive blood product as per standard of care at the hospital where their procedure is taking place.Patients in the ROTEM arm will receive blood product prophylaxis according to ROTEM cut-offs (see Fig. 1 above).

Data will be collected prior to the procedure, immediately post-procedure, 7 days post-procedure and 28 days post the procedure. Data will be collected from the patient directly via medical history taking and examination, and also from the hospital’s electronic medical records.

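### The plan rules out all covariate adjustment, so the pre-randomisation ROTEM algorithm result, a strong predictor of the primary efficacy outcome, goes unused and the valid crude comparison is less precise than it need be

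*Protocol article*

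**What the plan says.** All references are to the protocol article.

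- **Measured in both arms.** Intervention description {11a}: "All participants will have baseline pathology including standard coagulation testing and a ROTEM analysis".
- **Measured before allocation.** Participant timeline {13}: once the standard tests qualify the patient, "ROTEM analysis will be performed, and the patient will proceed to the randomisation phase".
- **Drives treatment in one arm.** ROTEM-based intervention: "ROTEM parameters will be used to determine whether pre-procedural blood product should be given". The text under Fig. 2 agrees: "Patients in the ROTEM arm will receive blood product prophylaxis according to ROTEM cut-offs".
- **That treatment is the outcome.** Outcomes {12}: the primary efficacy outcome is the proportion of procedures requiring prophylactic transfusion, "defined as the procedures before which any combination of FFP, platelets and/or cryoprecipitate is given to the participant".
- **Crude test.** Statistical methods {20a}: "The primary outcomes and secondary outcomes comparing proportions or percentages will be compared using chi-squared or Fisher’s exact tests".
- **No adjustment.** Additional analyses {20b}: "Given the RECIPE trial is an RCT, we are not adjusting for any variables".

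Allocation is stratified by procedural risk, platelet count and INR (Sequence generation {16a}), not by the ROTEM result.

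**The concern.** The reason given for not adjusting is mistaken. Randomisation makes the crude comparison unbiased on average, but it does not remove chance imbalance in a strong baseline predictor within one small trial. Removing the noise from that imbalance is what adjustment is for.

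This predictor is unusually strong. If the algorithm is followed, the yes/no result (product indicated or not) fixes the outcome of each ROTEM-arm patient. If nearly all controls are transfused, most of the random error in the estimate is then the share of ROTEM-arm patients who happen to be algorithm-positive. The control patients' ROTEM results estimate the same share and are not used. At stake are the width of the confidence interval and the power of the primary efficacy test. This is also a stated decision with a stated reason, not a detail left to an analysis plan.

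**Working it through.** **Inputs.** Sample size {14}: 30% reduction, 90% power, 5% alpha, 10% loss, 28 per arm. Statistical methods {20a}: two-sided test. The control rate and adherence to the algorithm are not stated, so they are assumed and varied. The entry rule ("If platelets and/or INR are within the range that the patient would normally be given FFP or platelet transfusion prior to the procedure") suggests a control rate near 100%.

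**Step 1: reproduce the plan's figure.** With p0 = 1.00, p1 = 0.70 and the unpooled formula:

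n = (1.96 + 1.282)² × [1.00×0 + 0.70×0.30] / 0.30² = 10.51 × 0.21 / 0.09 = 24.5, so 25 per arm. Then 25/0.9 = 27.8, so 28 per arm and 56 in total.

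This is the only two-sided reading tried that gives 56 in total after allowing for losses, so 100% v 70% is used as the planning case.

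**Step 2: variance formulas.** Let R be the algorithm result, n the number per arm and N = 2n.

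- Crude: Var = [p1(1−p1) + p0(1−p0)] / n.
- Standardised over R: Var = {2E[Var(Y1|R)] + 2E[Var(Y0|R)] + Var(E[Y1−Y0|R])} / N.

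Planning case, full adherence, n = 25:

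- Crude: 0.70×0.30/25 = 0.0084, SE 0.092.
- Standardised: (0 + 0 + 0.70×0.30×1²)/50 = 0.0042, SE 0.065.
- Ratio 2.0.

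**Step 3: four scenarios.** Let q be the share for whom product is indicated.

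- A: q = 0.70, full adherence, all controls transfused.
- B: q = 0.706, 5% non-delivery in both arms, 10% of algorithm-negative ROTEM patients transfused anyway.
- C: q = 0.733, 10% non-delivery in both arms, 15% transfused anyway.
- D: q = 0.70, ROTEM arm as A, 85% of algorithm-negative controls transfused.

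| | Control v ROTEM | N×Var crude | N×Var standardised | Ratio |
|---|---|---|---|---|
| A | 100% v 70% | 0.420 | 0.210 | 2.00 |
| B | 95% v 70% | 0.515 | 0.365 | 1.41 |
| C | 90% v 70% | 0.600 | 0.490 | 1.22 |
| D | 95.5% v 70% | 0.506 | 0.228 | 2.22 |

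With a 30-point difference and 5% or 10% deviation both ways in both arms, the ratios are 1.49 and 1.29. With controls at 100% and only the ROTEM arm departing from the algorithm, they run from about 1.4 to 1.75.

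**Step 4: power at 25 per arm, like for like** (exact calculation and simulation).

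| | Fisher → stratified exact | Uncorrected chi-squared → Cochran-Mantel-Haenszel |
|---|---|---|
| A | 81% → above 99% | 97% → above 99% |
| B | 55% → 70% | 71% → 78% |
| C | 31% → 39–40% | 45% → 47% |
| D | 58% → 93% | 74% → 98% |

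**Step 5: validity of the stratified tests.** In a simulated null (indicated patients always transfused, others 30%, same in both arms), rejection was 1.8% for the stratified exact test and 4.3% for Cochran-Mantel-Haenszel, so type I error is held.

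**Step 6: the interval.** In scenario A every arm-by-result cell is 0% or 100%. A variance that treats R as fixed is then zero and the interval has no width; in simulation it equalled the true value in only 12% of trials. The Step 2 formula, which includes the sampling of R, covered about 93% to 94% in scenarios A to D.

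**The case against.** The strongest reply is that nothing is invalid: an unadjusted intention-to-treat comparison of two proportions is unbiased with correct type I error, and declining to adjust is a legitimate choice. That stands. A reader might infer that the planned analysis is biased; the documents do not support that.

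A reader might also take a doubled variance, or a gain of up to 35 points, as a fact about this trial. Neither is established:

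- The ratio depends on a control rate and an adherence level that the documents do not give.
- The large gains are against Fisher's test. The plan also permits chi-squared, for which the planning-case gain is only about 3 points. Crossing the two comparisons misleads: in scenario C the stratified exact test (40%) falls below plain chi-squared (45%).
- Scenarios B to D have differences of 25, 20 and 25.5 points, not 30. Part of their low baseline power comes from the smaller effect, not from leaving out the covariate.
- At 28 per arm and 100% v 70%, unadjusted Fisher has 89% power and chi-squared 98%. If the reduction matched the earlier trials' 45% (100% v 55%), Fisher would have 99% even at 25 per arm.

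Timing also counts. Recruitment began in February 2021 and treating teams are unblinded, so a late change of primary test has a credibility cost. That is manageable, because the covariate is fixed before randomisation and the crude result would still be reported.

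These points limit the size claimed. They do not remove the gain: each stratified test did better than its crude counterpart in all four scenarios.

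**Conclusion.** The concern holds as one of efficiency, not validity. The rationale in {20b} is wrong, and it shuts out a baseline variable that is available in both arms at no extra cost. The variance ratio is 2.0 at 100% v 70% with full adherence, about 1.2 to 1.5 when both arms depart from their rules, and about 2.2 when some algorithm-negative controls are not transfused. The power gain at 25 per arm is about 8 to 35 points with exact tests and about 2 to 24 with asymptotic ones. All of this rests on assumed control rates and adherence. It also assumes that the algorithm in Fig. 1, which is not shown in the text at hand, reduces cleanly to product indicated yes or no. No such gain is shown for the bleeding outcome.

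**What to change.** Replace the sentence in {20b} and, before the data are analysed, pre-specify the following for the primary efficacy outcome:

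1. Derive the algorithm result (product indicated yes/no) from the pre-randomisation ROTEM values in both arms, without reference to allocation.
2. Make the primary test a Cochran-Mantel-Haenszel test stratified by that result, exact if counts are sparse. State the rule for choosing.
3. Report the marginal risk difference standardised over the result, with a 95% confidence interval whose variance includes the sampling variation of the result, for example one based on the influence function. Avoid a plain logistic model, which would face separation.
4. Keep the crude comparison as a supporting analysis.

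The cost is one derived variable and revised wording, with no extra patients, visits or tests. Two analyses of the primary outcome will be reported, and the change needs the DSMB and ethics approval that the section on protocol amendments {25} requires.

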## Assignment of interventions: allocation

### Sequence generation {16a}

Participants will undergo computer-generated randomisation using Study Randomizer [Software Application]. (2017) Available at: https://www.studyrandomizer.com. Allocation will be stratified according to procedural risk (low vs. high bleeding risk), platelet count (greater than or less than 30 × 10^9^/L) and INR (less than or greater than 2.0).

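### Allocation is stratified by procedural risk, platelet count and INR, but the plan rules out adjusting for them; the unadjusted test stays valid but is conservative to the extent that these factors predict transfusion

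*Protocol article*

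**What the plan says.** Under Sequence generation {16a}, the article says: "Allocation will be stratified according to procedural risk (low vs. high bleeding risk), platelet count" (cut at 30 × 10^9/L) and INR (cut at 2.0). Three binary factors give eight strata.

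Under Statistical methods for primary and secondary outcomes {20a}, it says: "The primary outcomes and secondary outcomes comparing proportions or percentages will be compared using chi-squared or Fisher’s exact tests". The threshold is two-sided 0.05, and no stratified form is mentioned.

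Under Methods for additional analyses {20b}, it says: "Given the RECIPE trial is an RCT, we are not adjusting for any variables". Both the decision and its reason are stated, so this is a fixed rule and not a detail left to an analysis plan.

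Two other sections bear on it. Standard of care intervention makes INR and platelet count the basis for transfusing control patients. Participant timeline {13} sends patients to randomisation only if their INR or platelets already fall in the local transfusion range.

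**The concern.** Stratified allocation balances the three factors between the arms, so differences in transfusion need between strata contribute little to the error of the treatment comparison. An unstratified test still counts those differences as noise. Its standard error is then too large, its true type I error falls below the nominal 5%, and power is lost. The stated reason does not meet this: that a trial is randomised supports unbiasedness, not leaving out the design factors. With 56 procedures in total, a few points of power may matter, and the strata are recorded in any case.

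**Working it through.** **1. The plan's own figure.** Sample size {14} states "Assuming a modest 30% reduction in pre-procedural prophylactic use of blood products", with 90% power, 5% alpha, 10% drop-out and 28 per arm. It gives no control rate and does not say whether the 30% is absolute or relative. Assume 100% v 70%, two-sided, unpooled variance:

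n = (1.960 + 1.282)² × [1.0 × 0 + 0.7 × 0.3] / 0.30² = 10.51 × 0.21 / 0.09 = 24.5, so 25 per arm.

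25 / 0.9 = 27.8, so 28 per arm and 56 in total. The stated size is reproduced at a 100% control rate.

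**2. Mechanism.** With stratum shares w_s and stratum rates p_s, the binomial variance in one arm splits as

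p(1 − p) = Σ w_s p_s(1 − p_s) + Σ w_s (p_s − p)².

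Stratified allocation largely removes the second term from the error of the arm difference. The unadjusted test keeps it.

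**3. Inputs to the simulation.** From the article: eight strata, 1:1 allocation, 28 per arm (all taken as evaluable), two-sided 0.05. Assumed: permuted blocks of 4; shares of 27.5% low risk (within the article's 25–30% cap), 30% with platelets below 30 and 40% with INR above 2; and a common odds ratio per factor of 1, 2.7 or 7.4. There were 8,000 runs per scenario. The adjusted analysis is a linear model with the three factors as main effects.

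**4. Power (%) for a 30-point difference**

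| Control v ROTEM | Odds ratio per factor | Chi-squared | Fisher | Adjusted | Adjusted − chi-squared |
|---|---|---|---|---|---|
| 100 v 70 | 2.7 | 98.3 | 92.8 | 98.2 | −0.1 |
| 100 v 70 | 7.4 | 98.7 | 94.3 | 98.7 | 0.0 |
| 95 v 65 | 2.7 | 86.4 | 79.2 | 87.7 | 1.3 |
| 95 v 65 | 7.4 | 87.2 | 80.0 | 91.3 | 4.1 |
| 90 v 60 | 2.7 | 77.1 | 69.6 | 79.6 | 2.5 |
| 90 v 60 | 7.4 | 79.0 | 71.7 | 86.6 | 7.6 |
| 80 v 50 | 2.7 | 67.8 | 60.0 | 71.3 | 3.5 |
| 80 v 50 | 7.4 | 68.5 | 61.1 | 79.7 | 11.2 |

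The gap from chi-squared to Fisher runs from 98.7 − 94.3 = 4.4 to 67.8 − 60.0 = 7.8 points.

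**5. Standard error.** In these scenarios the mean unadjusted SE divided by the true SE is 1.00–1.02 at odds ratio 2.7. At 7.4 it is 1.05 (0.0851 / 0.0812, 100 v 70) to 1.13 (0.1192 / 0.1058, 80 v 50).

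**6. Type I error, both arms at 70% or 85%.** Chi-squared: 3.4–4.2% at odds ratio 2.7 and 2.6–2.7% at 7.4. Adjusted analyses (main effects or Cochran-Mantel-Haenszel, CMH): 4.2–5.3%. A separate set of 2,500 runs per scenario gave 2.8–4.4% for chi-squared, hence the overall range of 2.6–4.4%. Fisher is conservative even with no prognostic factor (2.8–3.7%), so most of its deficit is its own discreteness and not the omitted strata.

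**7. Cost if the factors predict nothing (odds ratio 1).** Chi-squared / main effects / 8-cell CMH power: 98.3 / 98.0 / 97.3 at 100 v 70, 85.8 / 85.3 / 84.2 at 95 v 65, 76.9 / 76.7 / 75.5 at 90 v 60, and 66.6 / 65.8 / 64.6 at 80 v 50. Main effects cost under 1 point. CMH costs 1–2 points here and up to about 3 in the 2,500-run set.

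**8. Sparseness.** 56 / 8 = 7 procedures per cell on average. With the assumed shares, the smallest cell expects 56 × 0.275 × 0.30 × 0.40 = 1.8. An exact test over eight cells (4,000 runs) has a type I error of 2.6–3.4%. At odds ratio 2.7 its power is below plain chi-squared: 82% v 87% at 95 v 65, and 73% v 77% at 90 v 60.

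**The case against.** The strongest reply is that little is lost under the trial's apparent design. Patients are randomised only if they already meet the local transfusion range, and the control arm is transfused on the same tests, so a control rate near 100% is the natural reading. It is also the rate that reproduces 56. There, chi-squared and the adjusted analysis have the same power (about 98%). This stands, and the claim about power must therefore be conditional.

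The article also gives no strength of prediction. At odds ratio 2.7 the SE is barely affected, and only strong factors bring type I error down to about 2.6%. That stands too.

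A reader might infer more: that the planned test is invalid, that its type I error is well below 5% as a matter of fact, or that the trial is already short of its 90% power. The article supports none of these. The error is on the conservative side, the type I figure depends on assumed odds ratios, and at 100% v 70% power is 93–98% even with the planned tests.

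For bleeding the case is weaker. Procedures are classed by likelihood of bleeding, but Background and rationale says that INR does not predict procedural bleeding and that bleeding is uncommon overall.

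The reply does not rescue the stated reason. A control rate near 100% is not written into the plan, and local discretion over cut-offs makes a lower one possible.

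**Conclusion.** The point holds as one of efficiency, not validity. The article stratifies on three factors and then excludes them from the analysis for a reason that does not justify doing so. If the factors predict transfusion with odds ratios of 2.7 to 7.4 each, chi-squared has a type I error of about 2.6–4.4%. Its power loss against main-effects adjustment depends on the control rate: about 0 points at 100%, 1–4 at 95%, 3–8 at 90% and 4–11 at 80%. Choosing Fisher adds roughly 4–8 points for a largely separate reason. The odds ratios, stratum shares, block size and control rate are all assumptions. The direction does not depend on their exact values, but the size does. The balance favours adjusting: the possible gain is several points and the possible cost is under one.

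**What to change.** Before analysis, replace the sentence in {20b}, and the matching test in {20a}, with a rule along these lines: the primary efficacy comparison adjusts for procedural risk, platelet stratum and INR stratum, as randomised, as main effects, and reports an adjusted risk difference with 95% CI; the unadjusted test is a sensitivity analysis.

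The method must still work if every control procedure is transfused, where ordinary logistic regression would fail. A linear risk-difference model with robust or small-sample standard errors would do, as would an asymptotic Mantel-Haenszel risk difference. An exact eight-cell test should not be the fallback, since it brings back the conservatism. Stratification should not be required for the bleeding outcome, where events are likely to be few.

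The change costs a short edit and no new data. If the factors are not prognostic, it costs under 1 point of power with main effects, or up to about 3 points with eight-cell CMH.
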